# MANAGEMENT OF ADVERSE EVENTS

## Adverse events (i.e. complications) related to the procedures, or combination of preventive, diagnostic or therapeutic strategies and procedures within the scope of standard treatment practice (other than medication).

In the context of studies aiming to assess standard care, the medical strategies or procedures, associated with the study, correspond to standard practice and are implemented in compliance with their indications. The potential adverse events are therefore incidents related to standard patient management and are not required to be specifically reported by the study administrator.

This study does not incur any additional risks, and no adverse events are expected in relation to text messaging.

No events will be reported in the context of this study.

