### Insulin treatment: injections or pumps?

Two treatment procedures currently exist: syringes and insulin pumps.

Syringes and injector “pens” allow insulin to be delivered several times a day. The most widely used forms of insulin in a paediatric setting are rapid-acting insulin analogues, intermediate-acting insulin and slow-acting insulin analogues.

The most widespread regimens are as follows [17]:

- treatment regimen with two injections: mixture of rapid-acting insulin and intermediate-acting insulin prepared immediately before use in an insulin syringe, before breakfast and the evening meal.

- treatment regimen with three injections: an injection before an afternoon snack or before lunch is added to the treatment regimen comprising two injections.

- basal-bolus treatment regimen: a rapid-acting analogue injection before each meal and a slow-acting insulin analogue injection before bedtime.

Increasingly used in a paediatric setting, insulin pumps are portable devices which administer continuous insulin infusions. The insulin doses are adapted according to capillary blood glucose levels and glycated haemoglobin measured every 3 months.

The insulin pump replaces the multiple treatment injections using insulin “pens”, and thus has numerous advantages. However, monitoring of capillary blood glucose is very important as even minor pump failure can lead to a risk of ketoacidosis. In the event of pump failure, the body has no insulin stores and ketone bodies rapidly increase. The patient should react promptly in the event of unexplained hyperglycaemia. Hence, the patient should receive thorough therapeutic education beforehand and comply with instructions.

1.1.3 Acute complications.

Two acute complications are a cause for concern. Firstly, hypoglycaemia when insulin intake is excessive relative to the ingested carbohydrates. Symptoms typically include malaise, visual disturbances, sudden fatigue and abdominal pain.

Secondly, ketoacidosis is the complication feared in adolescents. This occurs when insulin intake is insufficient. In this situation, the cells are deficient in glucose, the main source of energy. The body then uses fatty acids to produce energy. In return, ketone bodies accumulate, leading to ketoacidosis.

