### Rationale for the modified Zelen design:

The primary endpoint is HbA1c level at 6 months. Changes in this level are related to patient compliance. One of the secondary endpoints (satisfaction, quality of life) is a patient-reported endpoint which, by definition, is totally subjective. A recent study showed that, in the absence of blinding, the treatment effect is overestimated for randomised trials with a subjective endpoint (Wood L, BMJ 2008). In order to limit bias related to the absence of blinding, we propose to use a modified Zelen design.

We will use the Zelen method while obtaining agreement to take part in two stages. All eligible patients and their parents will initially be invited to take part in a cohort study aiming to assess changes in diabetes control over a 6-month period. An information leaflet (IL1) on the study objectives and procedures will be given to the parents and young patients. Patients will be informed that they may choose not to take part in the study. Secondly, still during the first appointment, after the randomisation step, adolescents randomised to the interventional group, and their parents, will be invited to take part in a study assessing text messaging intervention. A second information leaflet (IL2) on the study objectives and text messaging intervention procedures will be given to the parents and young patients. Patients will be informed that they may choose not to take part in this study.

This method makes it possible to avoid the risks of bias due to the absence of blinding. In a conventional randomised trial, patients assigned to the control arm may modify their behaviour as they know they will not receive text messaging support.

This design is acceptable in this context for several reasons: The procedure for obtaining consent in two stages has already been used to assess rehabilitation, and several ethics committees have approved its use in this context (Quilty *et al*., 2003, Rannou, PHRC National in press, Forestier R, ARD 2009).

From a methodological perspective, the limitations of the Zelen design correspond to contamination risks due to refusal of intervention. In our study, the contamination risk should not be high in view of:

- The absence of risk related to intervention

- The short intervention time-frame

- Contamination risk in the standard management group is very unlikely as this text messaging intervention is not currently proposed outside the scope of this study.

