## FOLLOW-UP VISITS at 3 and 6 months (M3 and M6)

The following procedures will be performed during these visits:

- Clinical examination
- Blood samples for laboratory work-up (assay of HbA1c level)
- Collection of the capillary blood glucose diary
- Distribution of a second capillary blood glucose diary
- Completion of the quality of life questionnaire for all adolescents
- Collection of any adverse events
- Satisfaction survey for patients randomised to the text messaging arm at M6.

These visits will be held with the doctor who included the patient in the study, and at the usual treatment centre.

At the end of the visit, the investigator will send the information sheet for centralised data entry.

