## Adverse events related to the specific monitoring procedures introduced by the study

The specific monitoring procedures introduced by a study aiming to assess standard care only entail negligible risks and constraints for persons taking part in the study. Consequently, a procedure for managing adverse events is not required for this study. In this case, the endpoints will be recorded during a medical visit at 6 months. The study will not require any additional samples or imaging examinations. This study does not incur any additional risks, and no adverse events are expected No events will be reported in the context of this study.

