Appendix 4: 3 MONTH FOLLOW-UP DATA COLLECTION FORM

Impact of Mobile Phone Short Text Messages on the Glycaemic Control of Adolescents With Poorly Controlled Type 1 Diabetes.

Appointment date: …/.../... (dd/mm/yyyy)

1) Study data: to be completed by the coordinator

Patient code: |__|__|__| |__|__|__| |__| |__|

2) HbA1c level

Sampling date for second HbA1c level: …/.../... (dd/mm/yyyy)

Result: ….... %

3) Adverse event to be notified, comments:

…....................................................................................................................................................................

…....................................................................................................................................................................

4) Collection of the capillary blood glucose diary: yes no

Percentage of insulin injections recorded _ _%

5) Distribution and collection of the quality of life questionnaire: yes no

6) Distribution of the second capillary blood glucose diary: yes no

7) If the patient has been randomised to the text messaging arm:

Did s/he send a “STOP” text message yes no

If “yes”, date on which this text message was sent: …/.../... (dd/mm/yyyy)

If this is the case, in a single sentence, indicate the main reason given by the adolescent: ……………………………………………………………………….

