Appendix 5: 6 MONTH FOLLOW-UP DATA COLLECTION FORM

Impact of Mobile Phone Short Text Messages on the Glycaemic Control of Adolescents With Poorly Controlled Type 1 Diabetes.

Appointment date: …/.../... (dd/mm/yyyy)

1) Study data: to be completed by the coordinator

Patient code: |__|__|__| |__|__|__| |__| |__|

2) HbA1c level

Sampling date for third HbA1c level: …/.../... (dd/mm/yyyy)

Result: ….... %

3) Adverse event to be notified, comments:

…....................................................................................................................................................................

…....................................................................................................................................................................

4) Collection of the capillary blood glucose diary: yes no

Percentage of insulin injections recorded _ _%

5) Distribution and collection of the quality of life questionnaires: yes no

6) If the patient has been randomised to the text messaging arm:

Did s/he send a “STOP” text message yes no

If “yes”, date on which this text message was sent: …/.../... (dd/mm/yyyy)

If this is the case, in a single sentence, indicate the main reason given by the adolescent: …..…………….

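### Section 8 says no events will be reported, while section 5.3 and the M3 and M6 forms collect adverse events to be notified; the text should be reconciled and the two acute complications the protocol names recorded as such

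*Protocol*

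**What the plan says.** **Collection.** Protocol section 5.3 includes "Collection of any adverse events" among the procedures of the M3 and M6 visits. Item 3 of the 6-month form (Appendix 5) reads "Adverse event to be notified, comments", and the 3-month form (Appendix 4) has the same item. In both it is followed by blank lines only. The visit list in the synopsis, the flow chart table and Table 2 do not show adverse event collection.

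**Reporting.** Section 8.1 says that incidents of standard management "are not required to be specifically reported by the study administrator", that none are foreseen from the texts, and then: "No events will be reported in the context of this study". Section 8.2, on procedures introduced by the study, says that "a procedure for managing adverse events is not required for this study" and repeats the no-reporting sentence.

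**Why events matter here.** Section 1.1.3 names two acute complications: "hypoglycaemia when insulin intake is excessive relative to the ingested carbohydrates", and ketoacidosis when there is too little insulin. Section 3 describes the intervention as several daily reminders to inject, sent at the patient's usual injection times, with none concerning capillary glucose.

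**The concern.** Site staff are told in one place to collect events for notification and in another that nothing will be reported. They cannot tell what item 3 is for or how carefully to complete it.

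The trial tests prompts to inject insulin and takes lower HbA1c as its measure of success. A reader of the results will ask whether any fall in HbA1c came with more hypoglycaemia, and whether ketoacidosis became less frequent. The trial has a randomised control arm and two planned visits at which to ask. Taken literally, the section 8 sentence would keep even a descriptive answer out of the report. Taken narrowly, it would not, but a single free-text line per visit is a weak source for such an answer.

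**Working it through.** **Step 1: the two readings of the section 8 sentence.**

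- *Reported means notified to the administrator or an authority.* Section 8 then says no event is notified, while item 3 of both forms is labelled for events to be notified. The two texts conflict.
- *Reported means presented in the results.* Section 5.3 and the forms then gather information at two visits that section 8 keeps out of the report. Collection is not impossible, but it serves no stated purpose.

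The texts need reconciling on either reading. The sentence about the administrator that comes shortly before it in section 8.1 favours the first reading. The sentence itself carries no such limit.

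**Step 2: what the forms can supply.** Item 3 is free text, with no field for event type, date or number. Neither hypoglycaemia nor ketoacidosis is a named item in Appendix 4 or 5. A table built later would depend on what each clinician chose to write, in a trial that section 4.1 describes as open-label.

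**Step 3: how much by-arm data could show.** The denominator comes from section 12.1. Its base figure reproduces: 2 × (1.96 + 0.8416)² × 1.6² / 1² = 40.2, rounded up to 41 per arm. The 20% increase gives 41 × 1.2 = 49.2, and the protocol plans 50.

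With no events among n = 50 patients, the one-sided 95% upper limit is 1 − 0.05^(1/n) = 1 − 0.05^(1/50) = 0.058, or 5.8% per arm.

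The protocol gives no event rate, so the risks p below are assumptions, shown as a range. The chance of at least one event in an arm is 1 − (1 − p)^50. Power to detect a doubling (p against 2p, two-sided 5%) is Φ[(p − 1.96 × SE₀)/SE₁], where SE₀ = √(2 × 1.5p × (1 − 1.5p)/50) and SE₁ = √([p(1 − p) + 2p(1 − 2p)]/50).

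| Assumed 6-month risk | At least one event in an arm of 50 | Power to detect a doubling |
|---|---|---|
| 1% | 39% | 6% |
| 2% | 64% | 8% |
| 5% | 92% | 15% |
| 10% | 99% | 29% |

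Worked line for 10%: SE₀ = √(2 × 0.15 × 0.85/50) = 0.0714; SE₁ = √((0.09 + 0.16)/50) = 0.0707; (0.10 − 0.1400)/0.0707 = −0.565; Φ = 0.29.

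Unless events are rare, some will probably occur and be worth describing. A formal comparison would have little power across this range.

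**The case against.** The best defence is that section 8 deals with the management of events and refers to what the administrator must report. In that setting the disputed sentence most naturally means regulatory notification. This stands as a plausible reading and limits what can be claimed, but the wording still conflicts with the label on the forms.

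Four stronger inferences are tempting, and the document does not support them:

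- *The trial will certainly present no hypoglycaemia or ketoacidosis by arm.* This follows only from the literal reading.
- *The collected events will be discarded.* Section 10.1 requires protocol information to be entered in the case report form, section 11.1 has the data checked and the database frozen, and section 11.2 archives both. Nothing excludes item 3.
- *The lack of a by-arm safety analysis in section 12.2 is itself a fault.* A descriptive table is commonly left to the SAP, which was not available here. What matters is that such a table would contradict section 8 taken literally and would have only free text to use.
- *The exemption fails because texting is not standard practice.* Section 4.4.2 does say that "this text messaging intervention is not currently proposed outside the scope of this study", but it says so when discussing contamination. Table 1 (section 1.3.2) lists the texts among the procedures added by the study, and section 8.2 exempts those on a separate ground, negligible risk.

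It is also fair to note that the messages prompt injections already in the patient's regimen, and that reminders aim to reduce the missed insulin that leads to ketoacidosis. The document gives no figure suggesting an excess of either complication. The diaries in both arms have seven daily glucose entries and a comments field, so the trial is not wholly without information. The forms, however, extract from them only the percentage of injections recorded.

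**Conclusion.** The inconsistency is real and holds under either meaning of reported. Its consequence depends on the meaning. If the sentence concerns notification only, the protocol needs a clarification and the forms need better items. If it is applied as written, the trial could not describe by arm the two acute complications it names itself.

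The effect is limited to the description of harms. Any by-arm result would be descriptive, as the 5.8% limit with no events in 50 shows; that limit assumes all 50 patients in the arm are followed for events. The power figures rest on assumed risks. This is an inexpensive correction worth making, and it is not evidence that the intervention is unsafe.

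**What to change.** 1. Reconcile sections 8.1 and 8.2 with section 5.3 and item 3 of Appendices 4 and 5. Either limit the no-reporting sentence to regulatory notification or delete it, and make the item 3 label agree with the choice.
2. State in the protocol that events recorded at M3 and M6 will be tabulated descriptively by randomised arm.
3. Put hypoglycaemia and ketoacidosis on the existing M3 and M6 forms as named items, asked the same way in both arms, and keep the free-text line for anything else.
4. Show adverse event collection in the synopsis visit list, the flow chart table and Table 2.

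The cost is two extra lines on each form and one descriptive table, at visits already planned. The downside is that events will probably be few and no formal test is warranted. No change to the sample size or the primary analysis is needed.

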## Adverse events related to the specific monitoring procedures introduced by the study

The specific monitoring procedures introduced by a study aiming to assess standard care only entail negligible risks and constraints for persons taking part in the study. Consequently, a procedure for managing adverse events is not required for this study. In this case, the endpoints will be recorded during a medical visit at 6 months. The study will not require any additional samples or imaging examinations. This study does not incur any additional risks, and no adverse events are expected No events will be reported in the context of this study.

# DATA MANAGEMENT

## Right of access to data and source documents

### Access to data and confidentiality

The administrator ensures that the protocol and information leaflet intended for patients included in the study or their representatives stipulate that the investigators shall allow access to the documents and personal data strictly required for monitoring, quality control and audits of a study aiming to assess standard care, by personnel individually appointed for this purpose by the study administrator. The administrator also ensures that each person taking part in the study has not objected to allowing access to their personal data.

These activities must comply with strict confidentiality regulations. Personnel thus appointed for these purposes are bound by professional secrecy, notably under the conditions defined in Articles 226-13 and 226-14 of the French Penal Code, in the same way as the investigators themselves.

During and at the end of the study, data collected on the participants and transferred to the administrator by the investigators (or any other study personnel) shall be coded. Under no circumstances shall these data clearly display the names or addresses of the persons concerned, or any other identifiable information. Data will be collected on each patient from the case report form. Patients will be allocated a study-specific code number, indicating the centre, order of inclusion and the patients’ initials (surname and first name).

Telephone contact details for all patients will be forwarded to a call centre. The study inclusion number, telephone number (without the patient’s name and address) together with the text messaging dates and times will be recorded on a secure web platform, separate from the case report form, allowing the text messages to be scheduled within the time-frames stipulated by the protocol. This platform will be accessed via a login and password. The information given to the service provider, namely the patient’s telephone contact details and inclusion number, will not be stored by the service provider but will be destroyed after the last text message has been sent.

The study database will only contain medical data (taken from the patient’s medical record at inclusion, at 3 months and at 6 months).

### Source data and documents

The source data are taken from the medical records of patients included in the study

# QUALITY CONTROL AND QUALITY ASSURANCE

## Instructions relating to data collection

All information required by the protocol should be entered in the case report forms. The data should be collected as and when they are obtained, and recorded in the case report forms in a legible manner. All missing data should be coded.

## Quality control

The investigator shall allow access to the documents and personal data strictly required for monitoring, quality control and audits of this study, by personnel responsible for quality control and duly appointed for this purpose by the administrator.

The person(s) appointed by the administrator regularly visit each centre, during study initiation, once or several times during the study according to the frequency of inclusions, and at the end of the study. The following aspects will be reviewed during these visits:

- patient protection and safety,
- compliance with the study protocol, the procedures defined therein and currently applicable regulatory texts,
- quality of the data collected in the case report form: accuracy, missing data, consistency of data with source documents (medical records, appointment diaries, original laboratory results, etc.),

All visits will be described in a written monitoring report.

## Audit

An audit may be carried out at any time by persons appointed by the [administrator and](http://www.chusa.jussieu.fr/urcest/sous_cadre.php?fich=lexique/new_index.php?isphp=0&fich=ec/legislation/dispositionslegislativespromoteur.htm) independent of the persons in charge of the study. It aims to guarantee the quality of the study, the validity of the results and compliance with the law and current regulations.

Personnel responsible for managing and overseeing the study agree to comply with the requirements stipulated by the administrator and the competent authorities with respect to audits or inspections concerning the study.

Audits may apply to all stages of the study, from development of the protocol to publication of the results and archiving of the data used or generated in the context of the study.

# DATA PROCESSING AND ARCHIVING OF STUDY DATA AND DOCUMENTS

## Data processing and archiving of study data and documents

Data entry is organised in a case report form, and the personnel in charge of data entry are the investigators and their teams. The data entered will be periodically checked by one of the investigators to ensure there are no missing data or inconsistencies.

The data will be checked by a data manager. Any “queries” will be issued. Prior to statistical analysis, the data manager will freeze the database. This database, used for the statistical analysis, will be archived by the person in charge of the analysis or the computer analyst (printed or electronic format).

## Archiving of study data and documents

“Source” documents will be kept in the patient’s medical record and archived under the responsibility of Hôpital Necker (AP-HP) (administrator). In keeping with the recommendations issued by the French Data Protection Authority (CNIL), the patient’s identity and contact details will not be communicated with his/her medical data. The patient will be identified by his/her initials (surname and first name), centre number and study inclusion number. The documents specific to a standard care study will be archived by the investigator until the findings are published.

This indexed archiving will include:

- Copies of the mandatory opinion from the CPP (IRB/IEC)
- The successive versions of the protocol (identified by the version no. and version date)
- All correspondence with the administrator
- The completed and validated case report form for each subject included
- All appendices specific to the study
- The final study report originating from the statistical analysis and quality control
- The certificates from any audits that may have been carried out during the study
- The database used for the statistical analysis must also be archived by the person in charge of the analysis (printed or electronic format).

